**Abstract**

8

**Background:** Preterm labor is the leading cause of neonatal mortality and morbidity. Therefore, once preterm labor is diagnosed before 34 weeks of gestation, tocolytic therapy is initiated in an effort to prolong the pregnancy. Despite meticulous research for useful tocolytics, the medications that are available for this indication have been proven useful for only approximately two days, and searching for a more useful agent for labor arrest is imperative. It has been suggested that progesterone derivatives are useful in preventing preterm labor in women with cervical shortening or preterm labor in the past. However, the impact of progesterone has not been sufficiently tested for pregnancy prolongation after tocolytic therapy.

**Working hypothesis and aims:** Since progesterone derivatives are useful in preventing preterm labor in cases of risk factors or previous preterm labor, they will also show efficacy in pregnancy prolongation in women whose preterm labor was arrested following tocolytic treatment. The study aim is to evaluate the efficacy of vaginal progesterone for the prolongation of pregnancy after arrested pre-term labor.

**Methods:** Multicenter randomized controlled trial. Patients diagnosed with arrested pre-term labor following tocolytics at 24-34 gestational weeks will be randomly allocated to receive either vaginal micronized progesterone 400 mg/day (200 mg\*2/day) or no treatment. The primary outcomes are the mean number of days from enrollment to delivery and the rate of preterm delivery prior to 37 weeks of gestation. Secondary outcomes include need for additional tocolytic therapy, the rate of pregnancies prolonged for at least one week, neonatal complications, and admission to neonatal intensive care unit.

Assuming mean difference between the groups of 7 days  $\pm$  14 days a sample size of 64 women per group will be required (5% two-sided alpha, 80% power). This sample size is sufficient to detect a reduction from 50% to 25% in the rate of women who delivered prior to 37 weeks (5% two-sided alpha, 84% power). Considering 10% drop outs, 140 women will be required for this study (70 per group).

**Expected results:** Progesterone will be useful to prolong pregnancy after preterm labor was arrested with tocolytics.

**Importance:** This study has the potential to find a treatment to prevent preterm labor and thus to dramatically reduce neonatal morbidity and mortality.

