| Yet, the study methodology had potentially serious flaws; first, over 25% of                | 132 |
| participating women did not return the unused medication, and among those who did,          | 133 |

the authors stated that they could not be certain that they really administered it. 134  
 Second, the definition for threatened preterm birth included cervical length  $\leq 30$  mm 135  
 until 31 gestational weeks and/or positive qualitative fetal fibronectin test, which 136  
 serve more as screening markers for preterm labor than actual signs of threatened 137  
 preterm birth. Therefore studies with more strict inclusion criteria for preterm birth as 138  
 well as higher dose of progesterone should be performed. In the present study we 139  
 would like to investigate the effect of daily 400 mg vaginal micronized progesterone 140  
 for the prolongation of pregnancy after arrested pre-term labor. 141

142

**Study hypothesis:** Vaginal micronized progesterone will prolong the interval 143  
 between labor arrest with tocolytic therapy and the development of labor. 144

**Study outcomes** 145

**Primary Outcomes:** 146

1. The mean number of days from enrollment to delivery 147

2. The rate of preterm spontaneous delivery (defined as spontaneous labor or preterm 148  
 delivery following induction/cesarean section due to preterm premature rupture of 149  
 membranes prior to 37 weeks of gestation) 150

**Secondary Outcomes:** 151

*Obstetrics* 152

1. Number of days from recruitment to repeated preterm labor episode or 153  
 preterm premature rupture of membranes, up to 37 weeks of gestation 154

2. Pregnancy prolongation beyond one week 155

3. Need for repeated acute tocolysis 156

4. Number of hospitalizations and length of stay until 36.6 gestational weeks 157

5. The rate of preterm spontaneous labor (defined as spontaneous labor or 158  
 preterm premature rupture of membranes prior to 37 weeks of gestation) 159

160

161

|                                                                                                                                                                                                                                                                                                                                                                                                                |                                               |

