| 4. Fetal/neonatal death                                                                                                                                                                                                                                                                                                                                                                                        | 166                                           |
| 5. Birth weight and the rate of small for gestational age neonates                                                                                                                                                                                                                                                                                                                                             | 167                                           |
| 6. The rate of neonatal complications including transient tachypnea, RDS (respiratory distress syndrome), bronchopulmonary dysplasia, ventilatory support, supplemental oxygen, IVH (intraventricular hemorrhage), NEC (necrotizing enterocolitis), PDA (patent ductus arteriosus), retinopathy, neonatal sepsis, and congenital abnormalities not previously identified (specifically genital abnormalities). | 168
169
170
171
172
173
174 |
| Maternal                                                                                                                                                                                                                                                                                                                                                                                                | 175                                           |
| 1. The rate of chorioamnionitis and endometritis                                                                                                                                                                                                                                                                                                                                                               | 176                                           |

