| d. Suspected amnionitis during testing for eligibility– evidence of active infection including temperature $\geq 38.0^{\circ}\text{C}$ and uterine tenderness, foul-smelling vaginal discharge, maternal tachycardia of 120 beats per minute or greater, or sustained fetal tachycardia of 160 beats per minute or greater | 199
200
201
202
203 |
| e. Evidence of significant placental abruption (contractions and significant bleeding from placental origin)                                                                                                                                                                                                               | 204
205                      |
| f. Intrauterine fetal death diagnosed at the time of admission                                                                                                                                                                                                                                                             | 206
207                      |
| 2. Major fetal malformation                                                                                                                                                                                                                                                                                                | 208                             |
| 3. Known maternal allergy to progesterone                                                                                                                                                                                                                                                                                  | 209                             |
| 4. Current use of progesterone                                                                                                                                                                                                                                                                                             | 210                             |
| 5. Epilepsy                                                                                                                                                                                                                                                                                                                | 211                             |

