| • Nausea                                                                               | 304 |
| • Dizziness                                                                            | 305 |
| Severe adverse effects (e.g., anaphylaxis) will be reported to the Helsinki Committee. | 306 |
| Sample Size and statistics                                                      | 307 |
| Assuming mean difference between the groups of 7 days $\pm$ 14 days a sample size of   | 308 |
| 64 women per group will be required (5% two-sided alpha, 80% power). This sample       | 309 |
| size is sufficient to detect a reduction from 50% to 25% in the rate of women who      | 310 |
| delivered prior to 37 weeks (5% two-sided alpha, 84% power). Considering 10% drop      | 311 |
| outs, 140 women will be required for this study (70 per group).                        | 312 |
|                                                                                        | 313 |
| Patients' confidentiality                                                | 314 |
| Patients' personal information will be kept in sealed brown envelop separated from     | 315 |
| the CRF. Each patient will receive a code number written beside the patient name       | 316 |
| inside the aforementioned envelop. Only the patient's code will be written in the CRF  | 317 |
| form. All study data will be regarded in a locked closet inside a closed room.         | 318 |
|                                                                                        | 319 |

|                                                                                                                                                                                                                                                                                                                                 |                          |
|---------------------------------------------------------------------------------------------------------------------------------------------------------------------------------------------------------------------------------------------------------------------------------------------------------------------------------|--------------------------|

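### The listed second primary outcome scores an indicated preterm birth with intact membranes as a non-event, although the Abstract and the power statement count any delivery before 37 weeks

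*Protocol*

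**What the plan says.** The protocol describes its second primary outcome in three places.

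- **Study outcomes, Primary Outcomes, item 2:** "The rate of preterm spontaneous delivery (defined as spontaneous labor or preterm" "delivery following induction/cesarean section due to preterm premature rupture of" membranes, before 37 weeks. There are two ways to be an event: spontaneous labor, or an induced or cesarean birth for which PPROM was the reason.
- **Abstract, Methods:** "the rate of preterm delivery prior to 37 weeks of gestation", with no restriction on cause.
- **Sample Size and statistics:** the sample "size is sufficient to detect a reduction from 50% to 25% in the rate of women who" delivered before 37 weeks, with 84% power at 5% two-sided alpha. Again there is no restriction on cause.

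The first primary outcome is "The mean number of days from enrollment to delivery", also without regard to cause. After enrollment, the protocol collects "Fetal/neonatal death" (Neonatal, item 4) and "The rate of chorioamnionitis and endometritis" (Maternal, item 1) as secondary outcomes. Obstetric secondary outcome 5 is the rate of spontaneous labor or PPROM before 37 weeks. The design is open label with an untreated control group.

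**The concern.** A woman induced or delivered by cesarean before 37 weeks, with intact membranes and without labor, meets neither limb of item 2. The protocol provides no third category, so she stays in the denominator and is scored like a woman who delivered at term. The Abstract and the power statement would score her as an event.

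Two things follow. First, the outcome as defined is not the outcome that was powered. Second, whether a preterm birth counts depends on the reason recorded for it, and that reason is given by clinicians who know the allocation. If one arm had more indicated births or more fetal deaths leading to induction, its rate on the second primary would fall for a reason other than fewer preterm births.

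**Working it through.** **1. Can such births occur on study?** Suspected amnionitis is excluded only during eligibility testing and fetal death only as diagnosed at admission; both can arise later. The four removal criteria are refusal, loss to follow-up, new allergy, and an exclusion criterion discovered afterwards. None covers an indicated delivery, so the woman remains in the analysis.

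**2. How is one birth scored?** Take, for illustration, enrollment at 28+0 and a cesarean at 29+0 for chorioamnionitis with intact membranes and no labor.

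| Definition | Score |
|---|---|
| Primary 1 (days to delivery) | 7 days |
| Primary 2, Study outcomes | non-event |
| Primary 2, Abstract | event |
| Primary 2, sample-size section | event |

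**3. The stated power.** Inputs from the protocol: n = 64 per arm, p1 = 0.50, p2 = 0.25, two-sided alpha 5%. With p̄ the mean of p1 and p2,

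power = Φ{ [ |p1 − p2| − 1.96·√(2p̄(1−p̄)/n) ] / √( [p1(1−p1) + p2(1−p2)]/n ) }

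- p̄ = 0.375; 1.96·√(0.46875/64) = 0.1677
- √(0.4375/64) = 0.0827
- (0.25 − 0.1677)/0.0827 = 0.995, so power = 84.0%

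The stated 84% reproduces for any delivery before 37 weeks.

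**4. Power under the spontaneous/PPROM definition.** The protocol gives no rate of indicated birth, so the rows below are assumptions. All-cause rates are held at 50% v 25%.

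| Assumption | Spontaneous/PPROM rates | Power, 64 per arm |
|---|---|---|
| 10% of preterm births in each arm indicated | 45% v 22.5% | 77% |
| 20% | 40% v 20% | 70% |
| 30% | 35% v 17.5% | 62% |
| 2% of women in each arm, difference stays 25 points | 48% v 23% | 85% |
| 10% of women in each arm, difference stays 25 points | 40% v 15% | 90% |

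For the 20% row: p̄ = 0.30; 1.96·√(0.42/64) = 0.1588; √(0.40/64) = 0.0791; (0.20 − 0.1588)/0.0791 = 0.52, so power = 70%.

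The direction depends on the assumption. Power falls if the treatment lowers indicated and spontaneous births in proportion. It rises slightly if indicated births are equally common in both arms and the whole 25-point difference is in spontaneous births.

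**5. Weight of a single birth.** 1/64 = 1.56 percentage points of an arm's rate.

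**The case against.** A spontaneous-preterm-birth endpoint is legitimate. The study hypothesis concerns the interval to the development of labor, and the Introduction argues for a local effect on the myometrium. Two primaries that measure different things do not contradict each other merely for that reason. This stands, but it does not explain why the Abstract and the power statement name a different endpoint. An SAP may specify how competing events are handled and tabulated, so the absence of such rules is not held against the protocol. The outcome's definition, however, is fixed here.

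The affected group is also narrow, and this stands too. Chorioamnionitis after PPROM may fall under the PPROM limb. Significant abruption is described as involving contractions, so some of those births may count as spontaneous labor.

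A reader might infer three stronger things that the documents do not support.

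- *That the two primaries score every such birth as success and failure.* Primary 1 is continuous and has no failure threshold. A woman enrolled at 25+0 and delivered for an indication at 36+4 contributes 81 days; one enrolled at 34+0 and delivered at 37+0 contributes 21. The opposition holds for early indicated births, not for all.
- *That the false-positive rate is badly inflated.* With all-cause preterm birth at 50% in both arms, spontaneous rates of 40% v 35% or 40% v 30% would give p < 0.05 in 9.0% or 21.9% of trials (two-sided, so including the few results in the wrong direction). These scenarios need indicated births in 15% or 20% of the progesterone arm against 10% of controls. Nothing in the protocol supports such rates or such an imbalance.
- *That a harm would pass as efficacy.* Fetal/neonatal death and chorioamnionitis are reported separately, and primary 1 would register early indicated births as short intervals.

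**Conclusion.** The point holds as a problem of definition. Item 2 of the primary outcomes makes indicated preterm births with intact membranes and no labor non-events, while the Abstract and the power calculation count them, and primary 1 counts them as deliveries. The classification rests on a reason for delivery recorded without blinding, and an arm with more such births would show a lower rate.

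The misclassification follows from the wording and needs no assumption. Its size does: 1.6 points per birth at 64 per arm, and power of about 77–70% instead of 84% if 10–20% of preterm births in each arm are indicated. Under the equal-frequency assumption power would be 85–90%, so a loss of power is possible but not certain. No bias in favor of either arm is shown; the definition leaves room for one.

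**What to change.** Reconcile the Abstract, the Primary Outcomes list and the sample-size section by making the second primary outcome any delivery before 37+0, whatever the cause. That is already the wording of two of the three places and the endpoint behind the 84%. Keep the spontaneous/PPROM definition as a secondary outcome, alongside or merged with the closely similar obstetric secondary outcome 5, with indicated births treated as a competing event and tabulated by arm and reason.

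Adding only selected indications, such as fetal death and chorioamnionitis, to the current definition is not a good substitute. Other indicated births would stay non-events, and the result would be neither a spontaneous nor an all-cause endpoint.

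The cost is about one sentence in the outcome definition and one table. The reason for delivery is needed already to apply the present definition. The primary becomes slightly less specific to labor. If the sponsor in fact meant 50% v 25% as spontaneous rates, an equal 2–10 points of indicated births added to each arm (assumption) would give all-cause rates from 52% v 27% to 60% v 35%, and power of 83% to 82% at 64 per arm, so little is lost.

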| Whether the patient should receive repeated courses of tocolytics and/or betamethasone will be left to the discretion of the attending physician according to the departmental protocol.                                                                                                                                                                                                                                                                                                                                                                                                                                                                                                                                                                                                                                                | 277
278
279                                                  |
| Data collection                                                                                                                                                                                                                                                                                                                                                                                                                                                                                                                                                                                                                                                                                                                                                                                                                  | 280                                                                |
| Baseline Characteristics: Age, ethnicity, gravity, parity, gestational age at diagnosis of preterm labor, baseline cervical exam at time of diagnosis, and time of arrest will be collected as mentioned in the CRF.                                                                                                                                                                                                                                                                                                                                                                                                                                                                                                                                                                                                             | 281
282
283                                                  |
| Information regarding the study outcomes, mentioned above in the study outcome section, will also be collected.                                                                                                                                                                                                                                                                                                                                                                                                                                                                                                                                                                                                                                                                                                                         | 284
285                                                         |
| Study randomization                                                                                                                                                                                                                                                                                                                                                                                                                                                                                                                                                                                                                                                                                                                                                                                                              | 286                                                                |
| Randomization will be done by computerized software according to power calculation and the codes will be kept inside sealed envelopes. The randomization table will be stratified to 24.0-28.6 and 29.0-34.0 according to the day of tocolytic initiation.                                                                                                                                                                                                                                                                                                                                                                                                                                                                                                                                                                              | 287
288
289                                                  |
| Product description                                                                                                                                                                                                                                                                                                                                                                                                                                                                                                                                                                                                                                                                                                                                                                                                              | 290                                                                |
| In this study we will use the progesterone derivative micronized progesterone (Utrogestan 200mg×2 PV per day; BESINS Healthcare), which is approved for use during pregnancy, and was proved to be effective in preventing preterm labor in patients with previous preterm labor and cervical shortening.                                                                                                                                                                                                                                                                                                                                                                                                                                                                                                                               | 291
292
293
294                                           |
| The control group will not receive any treatment.                                                                                                                                                                                                                                                                                                                                                                                                                                                                                                                                                                                                                                                                                                                                                                                       | 295                                                                |
| Women who will be allocated to the treatment group will receive a prescription to purchase this medication from the pharmacy. The women will receive a refund for the cost of the medication after presenting the receipt from the pharmacy.                                                                                                                                                                                                                                                                                                                                                                                                                                                                                                                                                                                            | 296
297
298                                                  |

|                                                                                        |     |
|----------------------------------------------------------------------------------------|-----|
| Possible Adverse effects of micronized progesterone (200mg×2 PV per day)               | 299 |
| • Changes in appetite and body weight                                                  | 300 |
| • Leg edema                                                                            | 301 |
| • Hyperpigmentation                                                                    | 302 |
| • Breast congestion                                                                    | 303 |
| • Nausea                                                                               | 304 |
| • Dizziness                                                                            | 305 |
| Severe adverse effects (e.g., anaphylaxis) will be reported to the Helsinki Committee. | 306 |
| Sample Size and statistics                                                      | 307 |
| Assuming mean difference between the groups of 7 days $\pm$ 14 days a sample size of   | 308 |
| 64 women per group will be required (5% two-sided alpha, 80% power). This sample       | 309 |
| size is sufficient to detect a reduction from 50% to 25% in the rate of women who      | 310 |
| delivered prior to 37 weeks (5% two-sided alpha, 84% power). Considering 10% drop      | 311 |
| outs, 140 women will be required for this study (70 per group).                        | 312 |
|                                                                                        | 313 |
| Patients' confidentiality                                                | 314 |
| Patients' personal information will be kept in sealed brown envelop separated from     | 315 |
| the CRF. Each patient will receive a code number written beside the patient name       | 316 |
| inside the aforementioned envelop. Only the patient's code will be written in the CRF  | 317 |
| form. All study data will be regarded in a locked closet inside a closed room.         | 318 |
|                                                                                        | 319 |

|                                                                                                                                                                                                                                                                                                                                 |                          |
|---------------------------------------------------------------------------------------------------------------------------------------------------------------------------------------------------------------------------------------------------------------------------------------------------------------------------------|--------------------------|
